**Prevention of post-splenectomy sepsis (PSS) in patients with asplenia – The PrePSS study protocol**

# Background

The spleen is the largest lymphatic organ and plays a crucial role in linking innate and adaptive immunity. As a result, the absence of the spleen is associated with significant morbidity and mortality (1). Patients with anatomical asplenia (partial or total surgical removal of the spleen) or functional asplenia (loss of function of the spleen) have a significantly increased lifelong risk of severe invasive infections (2, 3). The mortality of post-splenectomy sepsis (PSS, also called overwhelming post-splenectomy infection [OPSI]), the most dangerous complication, reaches 30-50% (4). Studies report incidence rates of 7-8 infections requiring hospitalization per 100 patient-years and a post-splenectomy sepsis incidence of 1 per 100 patient-years. Compared to the general population, patients with asplenia have an approximately 6-fold increased risk of sepsis-related hospitalization (5).

The high mortality of these infections has led to guidelines for the prevention of sepsis in asplenic and hyposplenic patients. These recommendations include patient education, vaccinations, prophylactic and stand-by antibiotics, medical alert cards, travel advice and early treatment of animal bites (6, 7). Patients without a functioning spleen and their physicians should be educated about the everyday risk of overwhelming infections and the need of prompt recognition and treatment of infections.

Asplenic patients should receive pneumococcal vaccination, meningococcal conjugate vaccine, *Haemophilus influenza* type b conjugate vaccine and yearly influenza immunization. A stand-by antibiotic should be prescribed for emergency use (‘pill in the pocket‘). A smaller subgroup of patients (age < 5years, patients after a PSS episode) should obtain antibiotic prophylaxis, although there is no international consensus on when to discontinue prophylaxis. Patients should carry a medical alert that can inform physicians of the patient’s asplenia, optimally. Furthermore, travellers to high-risk areas, for example with regard to malaria, should secure optimal preventive measures. The effectiveness of these prevention measures has been shown in several studies (8-10).

Nevertheless, despite from these clear recommendations, previous studies have found poor adherence to preventive measures (2, 11). In a recent prospective multicenter cohort study from Germany (12), the vaccination status was queried in patients with PSS admitted to an intensive care unit. Only 21% of patients had been vaccinated in the past five years according to the recommendations for asplenic patients with a pneumococcal vaccine; only 6% had ever been vaccinated against meningococci and 12% against *H. influenzae*. Accordingly, only 12% of patients had received a seasonal influenza vaccination. In the asplenia registry study at the Medical Centre University of Freiburg, only 6% of patients treated as part of regular care by general practitioners had completed the vaccination schedule according to current recommendations (13). The registry data also show impressively that the booster immunization rates for each vaccine are again significantly worse than the primary immunization rates. In addition, only a minority (47%) of patients had received prescriptions for stand-by antibiotics.

Reasons for the lack of adherence to recommended prevention measures could be, on the one hand, that the prevention measures are unknown to patients and physicians (8). On the other hand, patients might not be aware of the increased risk of infections, which could explain the low adherence to preventive measures. Several studies suggest the ‘Health Action Process Approach‘ (HAPA) as a theoretical framework for the understanding of health behaviour in general (14-16) and for vaccination behaviour in particular (17-19). The HAPA postulates a two-phase approach to action: Firstly, a pre-intentional motivational phase, which is characterized by risk perception, expectation of action results and expectation of self-efficacy and leads to an intention. And secondly, a post-intentional volition phase, which comprises factors as planning, action control, social support, recovery self-efficacy and leads to the actual health behaviour. Situational barriers and resources also play a role here as they influence the intention, planning and health behaviour. Social support, for example, represents a resource and the lack of it could be a barrier to adopt and maintain health behaviour (20). Interventions to improve health behaviour beyond the passive provision of information material have not yet been described for asplenic patients.

Aim of the study is to improve the adherence to guideline-based preventive measures and thereby reduce the incidence of PSS by a novel telephone-based intervention that involves both patients and their general practitioners. By educating patients, the intervention contributes to the participation and empowerment of patients, who take responsibility for their own health in general and the implementation of prevention measures in particular. The new intervention is supposed to improve patients’ health by reducing morbidity as well as mortality and increase the quality-of-life of patients with asplenia. In addition, it can be expected that the costs of health insurance companies will decrease, since the treatment and follow-up costs of post-splenectomy infections are relatively high compared to the planned intervention and implementation of preventive measures. Evidence for this assumption can be found in cost-effectiveness analyses of PSS prevention in asplenia registries (12, 21). Furthermore, the development of such an intervention can serve as a model for other studies.

To the best of our knowledge, it is the first study that addresses the insufficient adherence to the prevention recommendations by the development and evaluation of a novel strategy that takes motivational processes into account and involves both patients and physicians.

Our assumption is that a targeted intervention strategy increases the adherence to recommended prevention measures.

**Methods**

**Aims and hypotheses**

The purpose of this study is to develop, manualize and evaluate a novel intervention that educates both patients and their physicians on appropriate preventive measures that should be undertaken to prevent infections after splenectomy. Besides information provision, the intervention is intended to motivate patients to implement the preventive measures and to convey action-related skills such as planning and managing barriers. It will be evaluated whether this targeted intervention (intervention group) is superior to usual care (historical control group) in terms of primary and secondary study outcomes. More precisely, we have put forward the following hypotheses as to the outcome of the intervention: (a) Adherence to infection-risk reducing preventive measures will significantly be increased (primary outcome). As a result, (b) the incidence of severe infections associated with asplenia (particular PSS) and (c) related health-care costs covered by health insurances will be reduced (distal secondary outcomes). (d) Risk perception, intention to implementation, perceived self-efficacy, action and coping-planning, positive and negative outcome expectations and received social support (HAPA-related variables) expected to account for the effect of the intervention will significantly be enhanced (proximal secondary outcomes). Furthermore, (e) disease knowledge, patients’ general and asplenia-specific self-management, asplenia-specific health literacy, patient involvement as well as health-related quality of life will significantly be enhanced (distal secondary outcomes).

Beside this quantitative outcome-evaluation, intervention patients’ and intervention patients’ physicians’ acceptance and evaluation of the intervention will be inquired in telephone interviews in a process-evaluating part of the study.

**Study design and setting**

This intervention study is designed as a prospective controlled, two-armed historical control group trial with baseline, post- and follow-up measurement and process evaluation (Figure 1). The combination of outcome and process evaluation meets the recommendations for evaluating complex interventions (22). As delaying the delivery of information on preventive measures puts patients on a non-justifiable risk (8) we decided against a randomized design and opted for a design with a historical control group for ethical reasons. In addition, the historical control group optimally illustrates current practice (‘usual care‘).

The study is conducted by the Medical Center - University of Freiburg, Germany (Division of Infectious Diseases, Department of Medicine II and Section of Health Care Research and Rehabilitation Research, SEVERA) and the AOK Baden-Württemberg, Germany.

Figure 1:

[figure not shown]

**Intervention**

The intervention comprises a telephone-based individual intervention session for patients with asplenia and a separate intervention for their general practitioner, conducted by study physicians of the Medical Center - University of Freiburg with expertise in clinical infectious diseases. The content of the intervention was developed based on comprehensive literature review, existing guidelines for infection prevention and the study physicians’ expert knowledge. Both, the intervention sessions for patients and for their physicians are manual-guided to ensure a consistent practice across all study physicians; however, the interview protocol is semi-structured to allow an individualized proceeding. When developing the manual, particular attention was paid to its practical feasibility to enable a future implication beyond this study.

Prior to the implementation of the intervention, all participants are sent patient or physician tailored educational materials with brief information on the prophylaxis options along with a comprehensibly prepared vaccination plan and a medical alert card for asplenic patients (5^th^ Ed.), which was developed by the Medical Center – University of Freiburg, the German Society of Infectious Diseases and the German Sepsis Society.

***Patient-directed intervention (intervention group)***

The 20-minute intervention session for patients in the intervention group is divided into an information-giving section and, following the HAPA theory, intervention components that promote motivation for initiation (risk perception, positive outcome expectancies and task self-efficacy) and planning (action and coping planning, maintenance self-efficacy) of recommended infection prevention measures. Applied behavioral change techniques according to Abraham and Michie (23) comprise: providing information about behavior-health link and on the benefits of preventive measures, providing instruction, prompting intention formation, specific goal setting and barrier identification, assisting with relapse prevention by teaching to use prompts or cues or plan social support and use of follow-up prompts.

In the first section patients are provided with evidence-based information on the immunological function of the spleen, on potential infections after the spleen has been removed (targeting risk perception) and are educated on the most important preventive measures (targeting positive outcome expectancies). These comprise receiving asplenia-specific vaccinations (pneumococcal, meningococcal and Haemophilus influenza type B) and annual influenza vaccinations. Moreover, patients are advised to have an emergency supply of ‘pill in the pocket‘-antibiotics to be taken in the event of sudden illness. The medical alert card for asplenic patients that informs health professionals about the splenectomy is introduced to them.

In the motivational-section patients are informed about the efficacy of the recommended preventive measures by means of a brief example on morbidity rates found to be higher among asplenic patients who are presumably unaware of their increased infection risk than among patients who received preventive education (targeting risk perception and positive outcome expectancies). Participants are sensitized to signs and symptoms that may indicate infection and are educated about the need of seeking rapid medical attention or taking emergency stand-by antibiotics if residing far from medical care and symptoms of infection occur (targeting task self-efficacy). In doing so, the information is framed in a way as to increase the awareness of the patient’s personal relevance rather than arousing fear of disease and it is focused on the feasibility of the recommended prevention behavior (24). After explanation, patients are encouraged to determine which recommendations they want to follow by ticking corresponding boxes on their worksheets to prompt goal-setting.

In the planning-section patients are told that the aim is to facilitate implementation of the previously set prevention goals by precise planning. They are asked to develop action plans defining when, where and how they would take the intended infection preventive measures, including necessary preparatory behaviors (e.g. making appointments, fill in the medical alert card by physician) (targeting action planning). Beyond that, participants are prompted to anticipate potential personal barriers to implementation of their personal plans. Amongst others, they are encouraged to think of situations in which the medical alert card could presumably be forgotten or circumstances that may led them failing to complete a vaccination course. At the same time, patients are assisted to find ways to attain their goals despite the identified impediments, for instance by seeking support from their networks (targeting maintenance self-efficacy and coping planning). To promote transfer into participants’ everyday lives they are encouraged to record their individual action and coping plans on designated worksheets accompanying the session.

At follow-up telephone call, all planned preventive measures are monitored and, when indicated, potential barriers to implement plans are discussed. If further assistance for implementation is assumed, participants are re-motivated and assisted to manage difficulties. Follow-up consultation is optional and individually tailored to the patients’ needs and not manual-based.

***Short version of the patient-directed intervention (historical control group)***

Patients in the historical control group receive a shortened version of the patient-directed intervention. The short version includes the information-giving section on the functioning of the spleen and on health implications of asplenia (targeting risk perception, outcome expectancy and task self-efficacy) as well as the motivational-section on the efficacy of the recommended precautions and on strategies for risk situations (targeting positive outcome expectancy and task self-efficacy) since it is important for ethical reasons that the control group is provided with the same precautionary information as the intervention group. However, the time-consuming planning-section is absent from the control group’s intervention as specific action plans and potential barriers are not discussed due to a lack of time resources. The intervention in the control group is implemented only for ethical reasons and is not an intervention variant to be evaluated. Data collection relevant for the study has already been completed in this group at the time of intervention implementation, thus a confounding influence on the outcome variables can be ruled out.

***Physician-directed intervention***

The physician-directed telephone intervention comprises evidence-based information on the consequences of asplenia and the increased infectious risk associated with high mortality rates. Attending physicians are educated about preventive measures consistent with current post-splenectomy guidelines including currently recommended vaccination and revaccination on the basis of given immunization schedules, indication of stand-by antibiotics and antibiotic prophylaxis. Furthermore, the intervention session includes an introduction in the purpose and use of the medical alert card and the necessity of patient education, particularly as to the patient-initiated antibiotic use in case of febrile illness. Physicians are advised to document any antibiotics in use and record a vaccine plan (vaccination status, need and interval for revaccination) specific to their patient using provided fields on the medical alert card.

The objective of the intervention is to heighten practitioners’ awareness and knowledge of available preventive measures to improve guideline-based post-splenectomy care. Thereby the information-provision component is the integral part of the physician’s intervention. However, in line with the patients’ intervention, the physicians’ intervention also targets risk perception, positive outcome expectancy and, subsequently, motivation to follow guideline recommendations. But practitioners are not obligated to do so and it is made sure that they do not feel restricted in their freedom of decision.

The intervention sessions take approximately 10 minutes. All participating physicians receive the intervention irrespective of the group allocation of their patients.

**Participants and recruitment**

Participants are patients with anatomic asplenia and their physicians (general practitioner or specialists). Eligible are German-speaking patients aged 18 years or older, who are insured by the cooperating health insurance AOK Baden-Württemberg, which is Germany’s 5^th^ largest health insurance and insures more than four million people.

Patient participants are preselected to either the intervention or control group based on the time interval since they underwent splenectomy. Patients who are recently splenectomized (at most 4 months) are allocated to the intervention group. Potential intervention patients are recruited about 6-8 weeks after splenectomy successively by biweekly request from February 2019 for a maximum period of 18 months. The historical control group consists of patients who are splenectomized since more than six months (at most 18 months). Thus, pre-interventional baseline-data on primary and secondary outcomes in the historical control group account for routine care. Potential control group patients were recruited at the start date of study implementation (January 2019) and, to attain the planned sample size, another cohort of patients was contacted half a year later (June 2019).

Potential patient participants are identified via a database search for all splenectomized patients within the predefined group-specific time periods since splenectomy by assistants of the AOK-Baden-Württemberg. Patients who meet criteria receive recruitment letters from the health insurance. Those who are interested in study participation receive detailed information on the procedure, the aims and the legal conditions of the study from the University Medical Centre Freiburg. Participants are asked to provide written informed consent and contact information if they agree to take part. Participants who participate in another clinical intervention trial at the same time are excluded from data analysis.

To identify potential physician participants, participating patients are asked to provide contact information on their general practitioner or other physician who mainly cares for their asplenia and sign an agreement releasing the practitioner form medical confidentially obligation. Physicians whose patients consent to having their physicians included in the study are recruited by letters with information concerning the study. No exclusion criteria for physicians are applied.

Both patient and physicians will receive a 30€ voucher for participation after study completion.

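### The intervention and control time windows are applied on different dates, and no rule keeps patients already invited to the intervention out of the June 2019 control call

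*Protocol*

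**What the plan says.** All of this is in Methods, Participants and recruitment.

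- Basis of allocation: "Patient participants are preselected to either the intervention or control group based on the time interval since they underwent splenectomy".
- Intervention limit: "Patients who are recently splenectomized (at most 4 months) are allocated to the intervention group".
- Intervention timing: candidates are "recruited about 6-8 weeks after splenectomy successively by biweekly request from February 2019 for a maximum period of 18 months".
- Control window: "The historical control group consists of patients who are splenectomized since more than six months (at most 18 months" being the upper limit.
- First control call: "Potential control group patients were recruited at the start date of study implementation (January 2019" is the date given. For the second, "another cohort of patients was contacted half a year later (June 2019".
- Search: candidates are "identified via a database search for all splenectomized patients within the predefined group-specific time periods since splenectomy".

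The section adds that control baseline data stand for routine care. Its only exclusion for double participation concerns a different clinical intervention trial, not the other group of this study.

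**The concern.** Group membership depends on elapsed time at the date of the insurer's search, and the two groups are searched on different dates. A patient can be recent enough for the intervention in February 2019 and, four months later, far enough from surgery for the June control window. The section intends exclusive groups but gives no surgery-date boundary, order of precedence or exclusion that would make them so.

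At stake is what the control group represents. Someone invited to the intervention and later contacted as a control has at least had a recruitment letter about asplenia. They may also have received the detailed study information or, if enrolled, the educational material and alert card described under Intervention. Carrying the card is itself scored in the primary outcome. Someone who ignored or declined the first invitation may differ in motivation, which plausibly affects an adherence score. The protocol does not mention prior invitation as a recorded variable, so the propensity score adjustment under Data analysis cannot be assumed to deal with it.

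**Working it through.** **Inputs.** The windows and months are those quoted from Participants and recruitment. From Sample size considerations: 360 to 400 splenectomies a year; 60% non-response and 50% dropout for controls, a yield of 0.4 × 0.5 = 0.20; 50% non-response for the intervention; expected analysis samples of 178 and 110; effect size 0.40, 80% power, two-sided 5%. The days of the searches are not given, so the first and last days of February and June are used as bounds.

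**The plan's own figure.** For an effect of 0.40, a two-sample t-test needs 99.08 per group, rounded up to 100. The stated minimum is reproduced and is not in dispute.

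**January 2019 control call.** Surgery falls between July 2017 and July 2018. There is no overlap with the intervention.

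**Overlap under the four-month limit.** It runs from (first intervention search − 4 months) to (June contact − 6 months).

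| First intervention search | June contact | Overlap starts | Overlap ends before | Days | Patients at 360–400 a year |
|---|---|---|---|---|---|
| 1 Feb | 1 June | 1 Oct 2018 | 1 Dec 2018 | 61 | 60–67 |
| 1 Feb | 30 June | 1 Oct 2018 | 30 Dec 2018 | 90 | 89–99 |
| 28 Feb | 1 June | 28 Oct 2018 | 1 Dec 2018 | 34 | 34–37 |
| 28 Feb | 30 June | 28 Oct 2018 | 30 Dec 2018 | 63 | 62–69 |

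Every combination overlaps: 34 to 90 days, about 34 to 99 insured patients (days × annual number / 365).

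**Overlap under the six-to-eight-week timing.** The earliest surgery date is 1 February minus 8 weeks, 7 December 2018. With June contact on the 1st, 15th or 30th the overlap is 0, 8 or 23 days, so at most 400 × 23 / 365 = 25 patients. If the first search was on 28 February, the earliest date is 3 January 2019 and there is no overlap.

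**Analysed controls affected, at the 0.20 yield.**

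- Four-month limit, all overlapping patients: 34 × 0.20 = 7 to 99 × 0.20 = 20.
- Four-month limit, only those who did not respond to the intervention invitation (50%): 34 × 0.5 × 0.20 = 3 to 99 × 0.5 × 0.20 = 10.
- Six-to-eight-week timing, all overlapping patients: 0 to 25 × 0.20 = 5.

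**Possible bias (assumption).** Suppose 10 of 110 controls are earlier non-respondents and score lower by 0.5 SD. The control mean shifts by 10/110 × 0.5 = 0.045 SD; with 1.0 SD, by 0.09 SD. The planned effect is 0.40. Earlier information would shift the mean the other way.

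**Power after exclusion (unadjusted t-test, effect 0.40).**

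- 178 against 105 (110 − 5): 90%.
- 178 against 90 (110 − 20, the extreme): 87%.
- If the stated rates are applied to 500 patients, the groups are 500 × 0.5 × 0.6 = 150 and 500 × 0.20 = 100. Losing 20 controls leaves 150 against 80: 82%.

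**The case against.** The best defence is that the six-to-eight-week timing describes how intervention patients were actually found, and that four months is only an outer eligibility limit. On that reading, patients operated on in October and November 2018 were too recent for the January control call and too late for the first intervention request, so June was their first invitation. The two streams then nearly adjoin, which fits the protocol's wording of membership in one group or the other and of a further cohort in June. This stands as a strong argument that the overlap is small and perhaps nil. It does not close the gap: both rules are stated, neither is said to govern the search, and a late-June contact still overlaps by up to 23 days.

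A reader might infer more than the documents support:

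- **That patients were entered in both groups.** Nothing shows this. The protocol only fails to rule it out.
- **That the effect is inflated by controls who refused the intervention.** Lower motivation in people who later agree to join is an inference, and prior information would act in the opposite direction. The net sign is not determined.
- **That excluding these patients leaves the trial underpowered.** The minimum of 100 assumes equal groups. With the larger intervention group expected, power stays above 80% even in the extreme case.
- **That control surgery dates should simply be cut at 1 October 2018.** Under the six-to-eight-week timing this would discard patients who were never invited to the intervention.

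**Conclusion.** The point holds as a gap in the allocation rule. Under the four-month limit an overlap is certain whatever the search days; under the six-to-eight-week timing it is confined to December 2018 and may not exist. Which size applies depends on the unstated search days and governing rule. The control counts also assume that people invited before respond at the plan's 20% yield. Any bias is probably small against the planned effect and of uncertain direction. It is still worth closing, because the comparison is not randomised and rests on controls who show undisturbed routine care.

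**What to change.** State in Participants and recruitment which rule drove the intervention search, the four-month limit or the six-to-eight-week timing, and give the search dates. State that nobody invited to the intervention counts as a control.

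The June call is reported as already made, so a filter on that search comes too late. Instead, match the June cohort against the insurer's list of intervention invitations, flag anyone invited earlier, exclude them from the control group in the primary analysis, and report how many there were. Restate the expected control number to match.

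The cost is one flag in the analysis data and the loss of a few controls: 0 to 5 under the six-to-eight-week timing, and 20 at the extreme under the four-month limit.
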